#### Outcome: Executive Function and Working Memory

Executive function has been proposed to have two core components: working memory and inhibitory control (Diamond, 2016). These two components, however, are relatively undifferentiated in children aged three to five years, such that they fall along a single factor and have been conceptualized as a unitary construct (Nelson et al., 2017). As such, we will measure executive function using the Head-Toes-Knees Shoulders (HTKS), which is a validated task that taps both working memory and inhibitory control (Cameron Ponitz et al., 2008, 2009; McClelland et al., 2014) and is compatible with the undifferentiated nature of executive functioning in early childhood (Garon et al., 2008). The HTKS had been found to have excellent inter-rater reliability and internal consistency in studies involving young children in Hong Kong (e.g., Chung, 2015; Chung et al., 2017; Liu et al., 2018).

The HTKS is administered as a two-part game in which children perform the opposite action to verbal commands. The first part of the game involves two commands (i.e., “touch your head” and “touch your toes”) and the second part of the game involves four commands (“touch your head,” “touch your toes,” “touch your knees,” and “touch your shoulders”). When a verbal command is given (e.g., “touch your toes”), the correct response by the child is the opposite (e.g., child touches their head); the children are asked to respond to the commands as fast as possible. There are four practice trials in each part of the game, during which the examiner demonstrates the correct response to each verbal command. There are 20 test trials, which are scored as 0 (incorrect action), 1 (initially incorrect, but self-corrected and finished the correct action), or 2 (correct action). As such, the total score ranges from 0 to 40. A ceiling rule will be applied, in which a child must earn at least four points in part one in order to progress to part two (Liu et al., 2018).

As the advantages of the error-reduced learning approach are believed to be associated with its relative lack of dependence on working memory (Maxwell et al., 2001), visuospatial and verbal working memory will also be measured. Visuospatial working memory will be measured using the backward Corsi block task (Pagulayan et al., 2006), and verbal working memory will be measured using the backward digit recall test (Alloway and Archibald, 2008). Backward tasks measure working memory because they require the storage of information while additional cognitive processing is required by reversing the sequence. Both of these tests have been used in studies of children (e.g., Bull et al., 2008; Gade et al., 2017; Capio et al., 2018). In the Corsi block task, the examiner taps on a sequence of cubes, while the child watches; the child will then be asked to tap the cubes in reverse sequence. The length of the sequence will start at two items, increasing by one cube after two trials at each length until the child fails to correctly reproduce the reversed sequence on two trials of the same length. In the digit recall test, the examiner will read a sequence of numbers starting from two items, and the child will be asked to recite the digit sequence in reverse. The length of the number sequence is increased by one item after two trials at each length, until the participant fails to recite the reversed sequence correctly on the two trials of the same length. A score of 1 will be given for every trial in which the child correctly taps or recites the sequence in reverse; the sum of scores represents the visuospatial and verbal working memory scores, respectively. The longest sequence that the participant tapped or recited in reverse represents the visuospatial and verbal working memory spans, respectively.

#### Outcome: Social Competence

Teachers will be asked to rate each child’s social competence in the classroom using the Social Competence and Behavior Evaluation Short Form (SCBE-30; LaFreniere and Dumas, 1996). The SCBE-30 is a validated measure of children’s affect modulation capacity, which includes 30 items that are rated on a 6-point Likert-type scale (1 is never and 6 is always). The items make up three subscales: anger-aggression (e.g., easily frustrated), anxiety-withdrawal (e.g., uneasy in a group), and social competence (e.g., takes pleasure in own accomplishment). The minimum raw score is 10, and the maximum score is 60 in each subscale. The SCBE-30 has been used in studies involving teachers of young children in Hong Kong and has been found to have good reliability and internal consistency (e.g., Chiu and Lau, 2018; Lam and Wong, 2018).

#### Covariates

Baseline measurements of height (cm) and body mass (kg) will be taken using standard portable stadiometer (SECA 213, SECA GmbH & Co. KG, Hamburg, Germany) and weighing scale (Tanita BF679W, Tanita Corporation, Tokyo, Japan), respectively, to calculate body composition. Fine motor skills proficiency will be assessed at baseline and at follow-up as a covariate because it has been shown to mediate the correlation between gross motor skills and cognitive development (Davis et al., 2011). A systematic review has also shown that fine motor skills are associated with working memory (van der Fels et al., 2015). The fine motor sub-scale of the Hong Kong Early Child Development Scale (Rao et al., 2013) will be used. Physical activity and sedentary behavior of participants will also be assessed at baseline and at follow-up as a covariate because these have been shown to be associated with motor proficiency of children (Logan et al., 2014). Further, Pesce et al. (2016) identified physical activity outside of school as a factor that mediates the effect of movement skills training on cognitive functions. Selected items from the parent-proxy Children’s Physical Activity Questionnaire (CPAQ; Corder et al., 2009) will be used, which include items that allow parents to report the amount of time that their child spent in moderate to vigorous intensity physical activities outside of school. CPAQ is being used in an ongoing study of child development in Hong Kong following standard procedures of translation and back-translation (Brislin, 1970); it has been found to have good internal consistency (Cronbach’s alpha = 0.762).

### Data Analysis

A two-group growth model for intervention studies (Muthen and Curran, 1997) will be fitted to the outcomes data. Growth curves will be fitted to the repeated measures with separate random intercepts and slopes estimated for the training and active control groups. The random intercepts capture individual differences in skills at commencement. The intercepts will be regressed on participant characteristics (i.e., sex, age, body composition, fine motor skills, and physical activity), with the latter acting as explanatory variables for the observed individual differences. A separate but parallel model will be estimated with the intercepts set at the final follow-up to examine the extent to which the same characteristics explain differences at that final data point.

Training effects will be evaluated using random slopes fitted to the data from the training and active control groups. For both groups, separate slopes will be fitted to describe (a) the normative growth observed and (b) growth that deviates from the normative pattern that can be attributed to training. Whether the mean of this second curve deviates significantly from zero serves as a test for the effects of training. Shared variance attributable to children belonging to the same class will be corrected for potential clustering effects by using the complex sampling procedure in Mplus 8.0 (Muthén and Muthén, 2017).

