From a theoretical perspective, it has been noted that motor development has been relatively neglected when trying to understand childhood behaviors (Rosenbaum, 2005; Iverson, 2010), even though movement enables exploration and expression. This may be due in part to limited evidence from robust experimental designs, which this present study aims to address. The aim of this study is to examine whether improved movement proficiency leads to benefits in the cognitive and social domains of child development. A fundamental movement skill training program, using the error-reduced learning approach, will be implemented and compared with typical kindergarten activities (i.e., active control). It is hypothesized that significant and meaningful improvements will be observed in gross motor skills proficiency from baseline to immediate and delayed time points following training; improvements will be greater among those in an error-reduced condition compared to those in the active control group. It is further hypothesized that improvements will be found in executive functioning and social competence from baseline to immediate and delayed time points following training; improvements will be greater for those who displayed larger gains in gross motor skills proficiency. Executive functions will be based on standardized tests of inhibitory control and working memory, while social competence will be based on standardized reports by teachers. Factors that could influence the main variables of interest will be accounted for.

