### Measures

To measure immediate and sustained effects of training on the outcomes, assessments will be performed prior to training (baseline, M1), at the end of the first term (mid-training, M2), at the end of the second term (post-training, M3), and four months after the end of training (follow-up, M4). Participants’ performances in the tests for fundamental movement skills, executive function, and working memory will be recorded on videos and scored post-hoc by designated research staff who were not involved in the test administration (i.e., blinded to participants’ allocation to training or active control groups). A random sample of video recordings (i.e., 10%) will be scored by a second set of designated research staff to establish inter-rater reliability.

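### As worded, the growth-model test of training is not an identified between-arm contrast, and it is not tied to the immediate (M3) and delayed (M4) effects hypothesised

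*Protocol article*

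**What the plan says.** The Data Analysis section of the protocol article names a two-group growth model for intervention studies, with a citation. It then specifies: "Growth curves will be fitted to the repeated measures with separate random intercepts and slopes estimated for the training and active control groups". On the training effect it says: "For both groups, separate slopes will be fitted to describe (a) the normative growth observed and (b) growth that deviates from the normative pattern", and the sentence goes on to ascribe that deviation to training. The test follows: "Whether the mean of this second curve deviates significantly from zero serves as a test for the effects of training". No other test of training is described.

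A second model is announced: "A separate but parallel model will be estimated with the intercepts set at the final follow-up to examine the extent to which the same characteristics". This model asks how far the covariates account for variation between children at M4. Its stated purpose concerns covariates, not a comparison of arms.

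The hypotheses, in Research Gap and the Present Study, are that "improvements will be observed in gross motor skills proficiency from baseline to immediate and delayed time points following training", and that "improvements will be greater among those in an error-reduced condition compared to those in the active control group". The Measures section gives the purpose of the four assessments: "To measure immediate and sustained effects of training on the outcomes". M4 falls four months after training ends.

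**The concern.** Two things do not fit together.

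1. The active control arm receives usual kindergarten activities, so it can have no growth due to the training programme. Yet the deviation slope is described for both groups, and slopes are estimated separately by arm. Nothing says that the normative slope is shared or that the deviation is zero in control. Without such a constraint, the mean of the second curve is not the randomised comparison. Children aged three to five develop over a school year whatever they are allocated to, so a growth term within an arm can differ from zero with no training effect at all.
2. The hypotheses concern change to two time points, one at the end of training and one after four months without it. The plan attaches one test of one mean to both. A significant result would not say whether the benefit was present at M3, at M4, or at both.

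At stake is whether the only stated test of training answers the questions the trial poses.

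**Working it through.** **The plan's own figure.** The section gives no number for this test. The nearest figure is the sample size in Participants, 144 for two groups at four testing points. It reproduces as a group-by-time test on 3 degrees of freedom: with f = 0.28, the noncentrality is 144 × 0.28² = 11.29 on 3 and 140 df, and power is 0.803. The article does not name the effect-size metric, so this is one reading. It does not correspond to a test of a single mean, but no stated number is wrong because of the present point.

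**Step 1: identification, same time scores.** Let g = 0 for control and 1 for training, with time scores t. The mean in arm g is

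μ_g(t) = α_g + a_g·t + b_g·t = α_g + (a_g + b_g)·t,

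where a is the normative slope and b the deviation. Only the sum a_g + b_g can be estimated in each arm.

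| Specification | Mean parameters | Rank | Identified? |
|---|---|---|---|
| a and b free in each arm (literal text) | 6 | 4 | No |
| a shared, b free in each arm | 5 | 4 | No |
| a and b both shared | 4 | 3 | No |
| a shared, b in training arm only | 4 | 4 | Yes |

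In the last row b is the training slope minus the control slope, which is the between-arm contrast that the hypothesis needs.

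**Step 2: different time scores.** Suppose a is linear and b has another shape s(t). Then b_0 and b_1 can each be estimated, but each is a component of growth within its own arm. If both arms follow the same curve α + a·t + c·s(t) with c ≠ 0, the mean of the second curve is non-zero and the training effect is nil. The relevant quantity is b_1 − b_0, which the text does not name.

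**Step 3: one test, two time points.** The shape of the deviation curve is not stated. For illustration, assume that it is one straight line, with M1 to M4 at 0, 5, 10 and 14 months (only the four months from the end of training to M4 come from the article). Set the true arm difference at 0, 0.5 and 1 for M1 to M3, in units of the M3 effect, and project by least squares.

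For an effect fully lost by M4 (0, 0.5, 1, 0):
- Equal baselines: slope = Σtd/Σt² = (2.5 + 10)/(25 + 100 + 196) = 12.5/321 = 0.0389. This implies 0.39 at M3 and 0.55 at M4.
- Separate intercepts: slope = (12.5 − 4 × 7.25 × 0.375)/(321 − 4 × 7.25²) = 1.625/110.75 = 0.0147, and intercept = 0.375 − 0.0147 × 7.25 = 0.27. Slope × time gives 0.15 and 0.21. Fitted values including the intercept are 0.42 and 0.47.

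| True M3, M4 | Equal baselines | Separate intercepts, slope × time | Separate intercepts, fitted value |
|---|---|---|---|
| 1, 1 (held) | 0.83, 1.16 | 0.76, 1.06 | 0.83, 1.14 |
| 1, 0.5 (half lost) | 0.61, 0.85 | 0.45, 0.63 | 0.62, 0.80 |
| 1, 0 (all lost) | 0.39, 0.55 | 0.15, 0.21 | 0.42, 0.47 |

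With times of 0, 4, 9 and 13 months, the first entry of the last row becomes 0.37, 0.54. In every row the line puts M4 above M3. A straight line with a positive slope can do nothing else.

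**Step 4: can four time points separate the two effects?** Yes. For the arm difference, the columns 1, min(t, t_M3) and max(t − t_M3, 0) have rank 3 of 3. With segment slopes δ₁ and δ₂, the effect is δ₁·t_M3 at M3 and δ₁·t_M3 + δ₂·(t_M4 − t_M3) at M4.

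**The case against.** The strongest reply is that the text describes a familiar model loosely. The section cites a two-group growth model for intervention studies, whose sensible use has control define normative growth and the added curve appear in training only. The deviation is ascribed to training, which an untrained arm does not have, and the test sentence speaks of one second curve in the singular. Constraints, loadings and curve shape are often left to an analysis plan, which is not shown here. A rank-deficient model would also usually reveal itself at fitting.

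Much of this stands. A reader might infer that the authors intend a wrong model, and the document does not support that. The non-identification result also depends on common time scores, which the text does not state.

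A reader might further infer that one curve over M1 to M4 cannot give both effects. That holds only for a straight line, and the article never says linear. A piecewise or freely loaded deviation would be consistent with the text and would separate M3 from M4.

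What the reply does not remove is that the article does make a statement about constraints, and that statement points away from the cited model: both slopes are assigned to both groups. Nor does it supply a link from the single test to the two hypothesised time points. The model centred on M4 does not do so, since its stated use is to explain differences by participant characteristics.

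**Conclusion.** The point holds as a fault in the stated specification, not as proof of a wrong intended model. Followed literally, the only stated test of training is either not identified (common time scores: six mean parameters, rank four) or not a between-arm contrast (different time scores). One reading repairs this, a shared normative slope with the deviation in training alone, and the text does not state it.

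Separately, the single test against zero does not deliver the two effects that the article hypothesises and says it measures. The figures for that limb are illustrative. They rest on an assumed straight line, assumed month spacing and assumed effect patterns. They show that under linearity M4 is always placed above M3, and that both are misstated when the effect fades. They do not show that the planned analysis will produce those values.

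**What to change.** State three things in the Data Analysis section.

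1. The normative slope is equal across arms, and the deviation is fitted in the training arm only, fixed at zero in control. Separate intercepts may stay as planned, since identification does not need them equal.
2. The deviation is piecewise, with one segment for training (M1 to M3) and one for follow-up (M3 to M4), and time scores in actual months.
3. The training-versus-control contrast is reported at M3 and at M4, so that each hypothesised effect has its own estimate and test.

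The cost is a few sentences, one extra mean parameter and a small loss of precision relative to a single slope. Because the slopes are random, a second deviation factor may also need variance or covariance restrictions: if normative growth is linear, its loadings are the sum of the two segments. If shared growth may itself bend at M3, the normative curve should have the same two segments. That adds one further mean parameter (six in all, still identified from the eight arm-by-time means) and keeps a common bend from being counted as a training effect.

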### Participants

A purposive sampling approach will be taken with the following inclusion criteria for participants: Children (1) aged three to five years, (2) enrolled in a local kindergarten within the same territory as the research center (i.e., New Territories and Hong Kong), and (3) have no diagnosed neurodevelopmental, medical, or orthopedic condition that is contraindicated to moderate intensity physical activity or that requires special educational needs support. In previous research, a six-week gross motor skills training program led to improved motor proficiency, with effect sizes ranging from 0.28 to 0.45 (Brian and Taunton, 2018). Taking a conservative approach, it was calculated that to achieve 80% power (two-tailed alpha at 0.05), with an effect size of 0.28, and accounting for between-group and within-group interactions, a total sample of 144 is required to compare two groups (i.e., training and control) at four testing points. Accounting for 10% potential attrition rate, 79 participants per group (*N* = 158) will be recruited. The participants will be randomly allocated as a group (i.e., one intact kindergarten class) to either training or active control. Typical kindergarten classes in Hong Kong have about 20 to 30 pupils; hence, three to four classes will be allocated to each group (i.e., training and active control). To control for a cluster effect and socioeconomic status being a potential confounder, we had recruited a local kindergarten with at least eight kindergarten classes from a middle-class area.

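### With only 6 to 8 randomised classes, the Mplus complex-sampling correction, taken as a class-level sandwich with a normal reference, gives the training test a type I error of about 10% to 18% instead of 5%

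*Protocol article*

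**What the plan says.** Under Participants, the Protocol article makes the class the unit of allocation: children are "randomly allocated as a group (i.e., one intact kindergarten class) to either training or active control". It gives the class size ("Typical kindergarten classes in Hong Kong have about 20 to 30 pupils") and concludes that "three to four classes will be allocated to each group", which is 6 to 8 classes in all. They come from one school: "we had recruited a local kindergarten with at least eight kindergarten classes from a middle-class area".

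Under Data Analysis, the training effect is tested by whether the mean of an additional growth curve, beyond normative growth, differs from zero. The only treatment of class is that shared variance is "corrected for potential clustering effects by using the complex sampling procedure in Mplus 8.0". The article names no small-sample correction, t reference, between-class degrees of freedom or permutation test. The limitations in the Discussion do not mention the small number of classes.

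**The concern.** A cluster-robust variance is a large-sample device, and the sample size that matters is the number of clusters. Here each arm has three or four. Training is assigned to whole classes, so the information about its effect lies between classes: classes minus 2 degrees of freedom, which is 4 with 6 classes and 6 with 8. A robust variance estimated from so few units is biased downwards unless it is corrected. It is also noisy enough that a normal critical value of 1.96 is too small even when the bias is removed.

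The same test serves gross motor skills, executive function, working memory and social competence. A result presented as significant at 5% and already adjusted for clustering would carry a false-positive risk at least about twice as large. The trial aims at causal conclusions and wider roll-out of the programme.

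**Working it through.** **The plan's own figure.** The article states no error rate for the cluster correction. Its one related figure is the sample size: "a total sample of 144 is required to compare two groups", from "to achieve 80% power (two-tailed alpha at 0.05), with an effect size of 0.28". This reproduces with a multivariate group-by-time test for independently allocated children: f = 0.28, numerator df 3, denominator df N − 4, noncentrality N × f² = 144 × 0.0784 = 11.29, power 0.803. The attrition step also fits: 144 × 1.10 = 158.4, that is, 79 per arm. The figure therefore contains no between-class component. That is a separate matter, but it means the stated 80% cannot be read as power for a class-level test.

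**Inputs.** From Participants: m = 3 or 4 classes per arm, C = 2m = 6 or 8, two-sided alpha 0.05. Assumed, because the article does not specify it: the procedure is a class-level sandwich with a normal reference. The finite-cluster factor c is also unstated, so three values are shown: 1, C/(C − 1), and m/(m − 1) within each arm.

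**Formula.** With equal class sizes, the sandwich variance has expectation (m − 1)/m × c times the true variance. Call this ratio r. The Wald statistic is then a t variable on 2m − 2 df divided by √r, so

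type I error = 2 × P(t on 2m − 2 df > 1.96 × √r).

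The average standard error relative to the true one is √r × k, where k is the mean of √(χ²/df): 0.940 on 4 df and 0.959 on 6 df.

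| Classes | Factor c | r | 1.96√r | Type I error | Times nominal | Mean SE / true SE |
|---|---|---|---|---|---|---|
| 6 | 1 | 0.667 | 1.600 | 18.5% | 3.7 | 0.77 |
| 6 | C/(C−1) | 0.800 | 1.753 | 15.4% | 3.1 | 0.84 |
| 6 | m/(m−1) | 1.000 | 1.960 | 12.2% | 2.4 | 0.94 |
| 8 | 1 | 0.750 | 1.697 | 14.1% | 2.8 | 0.83 |
| 8 | C/(C−1) | 0.857 | 1.815 | 12.0% | 2.4 | 0.89 |
| 8 | m/(m−1) | 1.000 | 1.960 | 9.8% | 1.95 | 0.96 |

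In the m/(m − 1) rows the variance is unbiased. The remaining inflation comes mainly from using 1.96 where the t critical value is 2.776 (4 df) or 2.447 (6 df).

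**Check on a growth model.** A four-wave, two-arm growth model was simulated under the null (20,000 runs per scenario), with equal and unequal class sizes and a class share of variance from 0 to 0.20.
- 6 classes: about 18% to 20% for the uncorrected sandwich and 15% to 16.5% with C/(C − 1).
- 8 classes: about 14% to 15% and 12% to 13%.
- A t reference combined with C/(C − 1) alone left about 6% to 7%.

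The rates barely moved with the ICC, so no outside value is needed.

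**What holds 5%.** A t test on class-level values gave 4.9% to 5.0% in a balanced simulation with 3 to 4 classes per arm. REML with Satterthwaite df gave 2.9% to 5.3%.

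**Cost in power (illustrative).** Read 0.28 as a standardised mean difference, take N = 144, and assume an ICC from 0 to 0.10. The standard error is √{(2/m)[ICC + (1 − ICC)/n]} with n = 144/C. At ICC 0 it is 0.167, so the noncentrality is 0.28/0.167 = 1.68 and power is 25% on 4 df or 29% on 6 df. At ICC 0.10 the standard errors are 0.303 and 0.274, and power is 11% and 14%.

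**The case against.** The strongest objection is that the article never states the variance formula, the finite-cluster factor or the reference distribution, so the inflation rests on an assumption about the software. This stands, and it is why the result is given as a conditional range. Within that assumption no factor rescues the test: the most favourable row is still about twice nominal.

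A second objection is that an unseen analysis plan may add a small-sample method, or that recruiting from one kindergarten controls the cluster effect. The article names its method, though, and that method does not suit the stated number of classes. A shared school does not remove class or teacher effects, and the inflation is present even at an ICC of zero.

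Three stronger readings are tempting and are not supported.
- A reader might infer that standard errors are uniformly about a fifth too small. Shortfalls of 17% and 23% belong only to the uncorrected sandwich. They are 11% and 16% with C/(C − 1), and 4% and 6% with the per-arm factor.
- A reader might infer that the growth model has more parameters than classes, so that a rank-deficient sandwich matrix invalidates the test. The training test concerns one parameter. Rank deficiency bears on joint tests and robust fit statistics and does not by itself invalidate a single standard error. The article also does not fix the growth form from which a parameter count would follow.
- A reader might infer that the latent growth model itself is wrong. The defect is in the inference, not in that model.

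**Conclusion.** The point holds and should be settled before analysis. Assuming a class-level sandwich with a normal reference, the two-sided type I error of the training test at nominal 5% is about 12% to 18% with 6 classes and 10% to 14% with 8, which is about 2 to 3.7 times nominal. The range reflects the unstated finite-cluster factor, not the ICC. The exact figures assume equal class sizes, and the unequal sizes simulated gave similar results. The calculations did not include the planned covariates, so extending the precise percentages to every adjusted model is an extrapolation, although the shortage of between-class degrees of freedom is the same for all outcomes.

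**What to change.** Base inference on the training effect on a small-sample method with classes-minus-2 degrees of freedom. Either of these will do:
- covariate-adjusted class-level changes compared by a t test; or
- a multilevel growth model with a class random effect, fitted by REML with Kenward-Roger or Satterthwaite degrees of freedom.

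The latent growth model may be kept for estimation if its training effect is given a per-arm-corrected variance and a t reference on between-class degrees of freedom. C/(C − 1) with a t reference is not quite enough. A class-level permutation test is no substitute at 3 versus 3: there are 20 allocations, so the smallest two-sided p is 2/20 = 0.10. At 4 versus 4 it is 2/70 = 0.029.

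Four classes per arm would be preferable to three, giving 6 rather than 4 df, and the recruited kindergarten has at least eight. This is a design choice and the fix does not depend on it.

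The analysis change itself costs little: revised wording and a different routine. The statistical cost should be stated openly. Critical values rise from 1.96 to 2.45 (8 classes) or 2.78 (6 classes) and intervals widen. Real power is well below the stated 80%: illustratively about 14% to 29% with 8 classes and 11% to 25% with 6, on the reading of 0.28 and the ICC range given above.
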